##### Stage 3: Insight Conversation

After the four-week Measurement Period, the participant has a face-to-face conversation with the investigator. The Booster report, based on the intensive ESM-surveys, is discussed and lifestyle goals are set using shared-decision making.

**Creating the Booster reportCreating the Booster report** A statistician, blinded to the participant, uses the intensive ESM surveys to compute an individual statistician report. This contains a summary of fatigue-sustaining factors and their dynamic networks. The summary includes fluctuations across the whole assessment period, averages for assessment hour and day of the week, differences for categorical factors, and day-to-day associations between paired ESM items across the Measurement Period. The dynamic networks (vector autoregression lag 1) are produced using Residual Dynamic Structural Equation Modelling. This method corrects for moving weekly average trends, weekend, and time of day and has been described more elaborately elsewhere [24, 48–50]. From all the generated output, the statistician and investigator independently select the most relevant summary figures and dynamic networks to be included in the Booster report (Fig. 3). Relevance is based on statistical significance, magnitude of standardised estimates, and assumed usefulness for the participant. Possible differences between selections are settled via discussion between the statistician and investigator.

**Fig. 3 Fig3:**
[figure not shown]
Example figures from Booster report. **A** Summary figure of fatigue intensity (y-axis) over the Measurement Period (28 days, x-axis). Blue dots are individual measurement points, black line is day average, red line is moving weekly average trend. **B** Dynamic network showing the time-lagged (3-h) relation between an increase in thinking hard first, followed by more fatigue, followed by less physical activity and more resting during the day

**Discussion of the Booster report with the participant** During the Insight Conversation, the investigator discusses the Booster report with the participant. The investigator presents findings in the report as hypotheses. The participant is consistently prompted to share their interpretation and the recognisability of the findings (e.g. “Based on your measurements, it seems like…., do you recognise that?”).

**Shared decision-making on lifestyle goals** The Booster report discussion initiates the shared decision-making on personal lifestyle goals aimed at increasing FSE. The report serves as a clinical tool for goal-setting, though goals may also arise from other topics discussed during the conversation. Goals are tailored to the patient-specific needs. Guided by the investigator, the participant formulates personal lifestyle goals in the Booster app’s Experiment Module as an implementation intention (Fig. 4) [51]. Only one active goal is allowed at a time. Additionally, a larger overarching goal, or “Dream” (e.g. fully participating at school or having fun with friends), can be added to motivate progress on smaller goals.

**Fig. 4 Fig4:**
[figure not shown]
Booster’s Experiment Module. **A** Goal setting with implementation intention. A participant can add a goal by formulating what specific behaviour (“Then”) they aim to perform when (“If”). In the schedule, the days of the week are selected on which goal evaluation will take place. **B** Goal evaluation. In the daily progress monitor, the participant reflects on goal attainment on the goal days. **C** Progress tracking. Daily progress monitor outcomes can be tracked

##### Stage 4: Experiment Period

In the twelve-week Experiment Period, the Booster app aids goal attainment with evaluations added to the daily progress monitor on self-selected goal days. If the active goal is not reached multiple times, the app proposes to change or adapt the goal. The participant can adapt the active goal or change it to another goal.

##### Stage 5: Evaluation Conversation

The Booster intervention concludes with the Evaluation Conversation. Guided by the investigator, the participant reflects on insights gained, goals achieved, and effects noticed. Future steps for continuing with Booster insights are considered.

### Criteria for discontinuing or modifying allocated interventions {11b}

Due to the negligible risk of the intervention, no criteria for discontinuing or modifying it were specified. However, in case of a participant’s deteriorating health, the investigator may decide to withdraw the participant.

### Strategies to improve adherence to interventions {11c}

In the Measurement Period, to sustain motivation for completing ESM surveys, participants receive coins for each survey they fill out. Bonus coins are awarded for achievements such as completing a streak of five surveys in a row, maintaining good compliance, or reaching time-related milestones (e.g., being two weeks into the Measurement Period). Bonus points are accompanied by a badge, and all collected badges can be viewed in the app. Points can be used in the in-app game. In the game, the participant pilots the avatar over an increasingly fast side-scrolling track by tapping the screen to avoid obstacles. In the game store, the participant can use the points to buy new track elements to create, for example, a longer, easier or prettier track. Additionally, the participant can create a daily diary post by selecting a sticker and/or writing things down. This results in a personal overview (Suppl. Table 2 d, Suppl. Fig. 3c).

In the Experiment Period, on the home screen, the app shows the active goal and its attainment. Besides, the Booster report becomes visible in the app. Also, the participant can track their own daily progress monitor outcomes.

Throughout the study period, participants will receive weekly reminders that they may contact the investigator for support. If a decline in adherence is detected, motivational messages will be delivered via the Booster app to encourage continued engagement.

### Relevant concomitant care permitted or prohibited during the trial {11d}

Participants are ineligible if they are already involved in a behavioural intervention targeting fatigue. However, they may receive concomitant fatigue-focused care if it is part of the patient-tailored Booster lifestyle goals. Participants may also continue with any medical or psychological care that began before the Booster intervention, provided the primary focus of this treatment is not on reducing fatigue.

### Provisions for post-trial care {30}

At the end of the Evaluation Conversation, the investigator identifies any ongoing care needs not addressed by the Booster intervention and ensures appropriate referrals are made.

### Outcomes {12}

The primary outcome of the study is FSE. Other outcomes are fatigue severity, school participation, life satisfaction, and perceived health (see “Plans for assessment and collection of outcomes”).

### Participant timeline {13}

Baseline assessment (T0) will take place ten to eighteen days before the Start Conversation (T1, Fig. 1). In this interim period, the participant starts filling out the daily progress monitor via the Booster app, which continues until the Evaluation Conversation (T3). From the start of the Experiment Period onwards (T2 to T3), marked by the Insight Conversation, goal attainment is evaluated as well via the Booster app (see sections “Stage 4: Experiment Period” and “Goal attainment”). Follow-up with elaborate questionnaires (see section “Demographics and potential covariates”, Suppl. Table 6) takes place three, six, and twelve months after the Insight Conversation (T2). Baseline and follow-up questionnaires will be filled out in the web-based survey portal KLIK (www.hetklikt.nu) (Fig. 1 and Suppl. Table 3).

### Sample size {14}

The power to detect an intervention effect with a multiple baseline design (RQ1) depends on the autocorrelation of consecutive daily progress monitor measurements, the start moment range, the number of repeated measurements, the intervention effect, and the number of cases [52]. In the earlier PROfeel study [48], the median autocorrelation of weekly measurements was 0.17 for FSE, 0.30 for fatigue severity, and 0.09 for QoL. Median autocorrelation of the five times daily ESM item on fatigue severity was 0.37 [48]. We expect the daily measurements in this study to show a higher autocorrelation than weekly measurements, but lower than a five times daily item. Thus, we assumed the autocorrelation in our study to be 0.30 across outcomes. The start moment range is nine, as the Booster intervention is randomised to start (T1) ten to eighteen days after the start of the daily progress monitor (T0). With 100% compliance, the number of repeated measurements is 130. With the abovementioned assumptions and inclusion of twenty cases, with up to 30% of daily measurements missing, the multiple baseline single-case randomisation test (SCRT) can detect medium to large intervention effects of ≥ 0.7 with a power of ≥ 0.80 at the group level (RQ1, Table 1). However, we anticipate small intervention effects since Booster is an early intervention, not treatment. The SCRT, used in SCED, has limited power to detect such small intervention effects [37, 52, 53]. In contrast, the permutation distancing test (PTD), developed for testing differences in means in single-case observational designs (SCODs), exhibits higher statistical power [53]. It is important to note that SCOD cannot establish causality. With the abovementioned assumptions, with up to 40% of daily measurements missing, the study is well powered to observe changes in outcomes for effect sizes as small as 0.3 at the single-case observational level (RQ2, Table 1).

**Table 1 Tab1:** Power for detecting intervention effects at the group and single-case level

Factors influencing power	Study design	
Autocorrelation (%)	30	
Repeated measurements (*n*)	130	
Power (%)	≥ 80	
Cases (*n*)	20 (group level)	1 (single-case)
Test	Multiple baseline SCRT	PDT
Start moment range (*n*)	9	NA
Maximum percentage missing data to retain sufficient power (%)	30	40
Minimum detectable effect size	0.7 (medium to large)	0.3 (small)

At the single-case level, intervention effect sizes are defined as small if 0.00–0.99, as medium if 1.00–2.49, andas large if ≥ 2.50 [54]

*Abbreviations: NA* is not applicable, *PDT* is permutation distancing test, *SCRT* is single-case randomisation test

For 80% power in detecting change points (RQ3), fifty measurements are needed, including at least six post-change points (start Phase B) [55]. For every outcome, the number of Phase A measurements is at least 42 (six weeks) if 100% compliant (see section “Statistical methods”). For detecting change points specifically, change points up until six days before the end of the daily progress monitor can be detected. The start of the daily progress monitor ten to eighteen days before the Start Conversation (T1) enables us to detect whether the Start Conversation itself or the Measurement Period (T1 to T2) coincides with a change point (Suppl. Figure 1).

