However, the study faces several challenges. First, in order to mirror the heterogeneous clinical practice, the inclusion criteria are broadly defined, with a low fatigue severity threshold of ≥ 15 points with the pSFQ. This corresponds to the upper 50th percentile of children with a chronic health condition) [45]. This may result in a diverse group of participants, limiting result replication. Nevertheless, this approach acknowledges the large intra-individual differences in fatigue and thereby strengthens the ecological validity of our results. Also, the additional analyses at the single-case level will shed light on intra-individual differences (RQ2 and 3). Ultimately, our study aims to identify the value of the Booster intervention for adolescents with a chronic health condition who experience hindrance by fatigue.

Second, the study is only powered to demonstrate causal medium to large intervention effects at the group level (RQ1),[37, 52] while one might expect smaller effects. Nevertheless, these smaller intervention effects can be observed with the PDT at the single-case level (RQ2), albeit without causal inference. However, if effects are replicated across individuals and also align with the timing of specific Booster intervention stages, the results of the PDT build a case for treatment efficacy, making alternative causal explanations less likely [39].

Third, we must consider the potential detrimental effect of intensive longitudinal data collection. While most participants in ESM studies reported heightened awareness from repeated measurements as positive, some experienced adverse effects [50, 75–77]. Repeated self-reflection can lead to effective cognitive processing and problem-solving but may also increase internalising symptoms [78]. In our study, intensive longitudinal data collection occurs through ESM surveys during the four-week Measurement Period and the daily progress monitor throughout. It serves both treatment and research purposes. We carefully balanced measurement burden (e.g. minimising items, personalised timing, distraction options in the Booster app, and contact with the investigator, exploring long-term effects with pre-post design instead of extending the daily progress monitor) with validity and scientific rigour (e.g. personalised Booster reports, single-case insights, validated items with strong psychometric properties, and sufficient measurements for statistical power).

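### The 80% single-case power stated for an effect of 0.3 is not reproducible from the plan's own inputs; the effect detectable in one case is about two to three times larger

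*Protocol article*

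**What the plan says.** Sample size {14} expects small effects and says that the group-level randomisation test (SCRT) has limited power for them. It turns to the PDT, applied to one person at a time, and concludes that "the study is well powered to observe changes in outcomes for effect sizes as small as 0.3 at the single-case observational level". Table 1, titled "Power for detecting intervention effects at the group and single-case level", gives the PDT column as one case, power of at least 80%, up to 40% missing and a minimum detectable effect of 0.3.

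The inputs are in the same section: "With 100% compliance, the number of repeated measurements is 130"; "we assumed the autocorrelation in our study to be 0.30 across outcomes"; and, in the paragraph on change points, "the number of Phase A measurements is at least 42 (six weeks) if 100% compliant". The Table 1 footnote says that at the single-case level "intervention effect sizes are defined as small if 0.00–0.99, as medium if 1.00–2.49", with large starting at 2.50.

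The statistical methods for RQ2 define the PDT statistic as a change in mean level between Phase A and Phase B. The methods for RQ4 form responder and non-responder groups from a significant PDT difference in fatigue-related self-efficacy (FSE). The Discussion, on its second challenge, says that "these smaller intervention effects can be observed with the PDT at the single-case level (RQ2), albeit without causal inference".

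**The concern.** A shift of 0.3 standard deviations is hard to detect with 130 independent values, let alone with 78 autocorrelated ones (130 × 0.60). A claim of 80% power there looks too good, and Table 1 rules out pooling as the explanation because it specifies one case.

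The figure carries weight. It is the only number behind the statement that small effects, which the SCRT may miss, can still be seen in individuals. It also bears on RQ4, where responder status is fixed by PDT significance for FSE alone. If power at 0.3 is nearer one in five than four in five, most participants with a true change of that size would fall in the non-responder group, and the comparison of characteristics would be blurred.

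**Working it through.** **Inputs from the protocol.** 130 daily values; autocorrelation 0.30; up to 40% missing; one case; statistic = Phase B mean minus Phase A mean; 42 Phase A days, hence 88 Phase B days, for FSE. The RQ1 methods add lags of four and six weeks for the other outcomes, so Phase A is 42 + 28 = 70 or 42 + 42 = 84 days (splits 70/60 and 84/46).

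**Assumptions, because the protocol does not state them.** 0.3 is the mean shift divided by the within-person standard deviation; alpha is 0.05, shown one-sided and two-sided; autocorrelation is first-order autoregressive; missing days fall at random; normal approximation.

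**Formulas.** With a fraction q of days observed and autocorrelation ρ:
- SE ≈ √[F × (1/nA + 1/nB)], where nA and nB are observed days and F ≈ 1 + 2qρ/(1 − ρ)
- one-sided power ≈ Φ(0.3/SE − 1.645); two-sided power ≈ Φ(0.3/SE − 1.960), plus a negligible opposite tail
- effect detectable with 80% power = (1.645 + 0.842) × SE one-sided, (1.960 + 0.842) × SE two-sided

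**The plan's figure.** I could not reproduce 80% for one case at 0.3. With independent values and equal phases, 80% power needs 4 × (2.487/0.3)² ≈ 275 values one-sided or 4 × (2.802/0.3)² ≈ 349 two-sided. The plan has 130, or 78 with 40% missing.

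**Best conceivable case** (65/65, no autocorrelation, nothing missing). SE = √(2/65) = 0.175; 0.3/0.175 = 1.71. Power = Φ(0.065) = 53% one-sided, Φ(−0.25) = 40% two-sided. Relaxing alpha to 10% one-sided gives 67%.

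**FSE, complete data** (42/88, ρ = 0.30). F = 1 + 0.6/0.7 = 1.857; SE = √[1.857 × (1/42 + 1/88)] = 0.256. The full correlation matrix, which also counts correlation across the phase boundary, gives 0.253. Power is 32% / 22%; detectable effect 0.63 / 0.71.

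**FSE, 40% missing** (25.2 and 52.8 observed days). F = 1 + 2 × 0.6 × 0.3/0.7 = 1.514; SE = √[1.514 × (1/25.2 + 1/52.8)] = 0.298 (full matrix 0.296). 0.3/0.298 = 1.007. Power = Φ(−0.638) = 26% one-sided, Φ(−0.953) = 17% two-sided; detectable effect 0.74 / 0.83.

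**Other splits, 40% missing, ρ = 0.30** (full matrix):

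| Phase A / B days | Power one-sided | Power two-sided | Detectable effect, one- / two-sided |
|---|---|---|---|
| 38 / 92 | 26% | 17% | 0.76 / 0.85 |
| 42 / 88 | 26% | 17% | 0.74 / 0.83 |
| 46 / 84 | 27% | 18% | 0.72 / 0.81 |
| 70 / 60 | 29% | 19% | 0.69 / 0.78 |
| 84 / 46 | 27% | 18% | 0.72 / 0.81 |

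The 38 and 46 rows are the extremes for FSE: 10 or 18 days to the Start Conversation plus the 28-day Measurement Period.

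**Other readings of 0.3.** Read as Cohen's f or as a correlation, 0.3 corresponds to a mean difference of about 0.60 to 0.63. With ρ = 0.30 and 40% missing, power is then 53–62% two-sided and 65–74% one-sided, still below 80%.

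**Does the PDT itself do better?** In a simplified simulation of a permutation test (ρ = 0.30, 40% missing), versions using time-spaced subsets reached at most about 14%. The version ignoring autocorrelation reached 27–40%, with a false-positive rate of about 9–12%. This is not the published algorithm, so it supports the calculation above but does not replace it.

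**The case against.** The strongest reply is that the metric is inferred. The protocol gives no effect-size formula, alpha or sidedness for the PDT figure. The footnote scale carries the citation used for the interrupted time series analysis, not the one used for the PDT. Table 1 also calls 0.7 medium to large in the group column, although the single-case scale would call it small. The simulation behind 0.3 may lie in a source that is not shown. This stands as a reason to state the reading as an assumption and to say not reproducible rather than impossible. It does not rescue 0.3, since the alternative readings tried also stay below 80%.

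A second reply is that RQ2 is secondary and exploratory, and that enrolment and the RQ1 test do not depend on this figure. That is correct and limits the consequence.

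A reader might go further and infer three things that the document does not support:
- **That nothing is left for small effects.** The plan's small band runs to 0.99, and effects of about 0.65 to 0.85 within it reach 80% power. The Discussion also appeals to replication across individuals and alignment with intervention stages.
- **That all single-case questions inherit the problem.** RQ2 uses the PDT together with the time series analysis, and RQ3 selects cases on either. Only the RQ4 grouping rests on the PDT alone.
- **That the investigators would read a null PDT as proof of no change.** The protocol nowhere says so; RQ2 is described as exploring change.

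**Conclusion.** The single-case power statement is wrong as written on any standard reading tried. Under a within-person standardised mean difference tested at 5%, power at 0.3 with 40% missing is about 26% one-sided or 17% two-sided for FSE, and at most about 29% or 19% for the other outcomes. The ceiling with every adverse condition removed is 53% or 40%. The effect that one case can detect with 80% power is about 0.63 or 0.71 with complete data, and about 0.7 to 0.85 with 40% missing.

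The exact percentages depend on the assumed alpha, first-order autocorrelation and random missingness. Over the phase splits above and a cruder variance inflation (15% / 23% for 42/88), they range from about 15% to 29%, so the conclusion does not change. What fails is the stated reach down to 0.3, and with it the use of a single PDT to call someone with a change of that size a non-responder. The PDT analysis keeps its value for larger effects.

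**What to change.** - In Table 1 and the Sample size text, replace 0.3 with the achievable single-case value (about 0.63 one-sided or 0.71 two-sided with complete data; about 0.7 to 0.85 with 40% missing). State the effect metric, alpha, sidedness and missing fraction beside it. If 0.3 came from a simulation on another metric, define that metric and show that it yields 80% under these inputs.
- Remove the claim of being well powered down to 0.3.
- Qualify the Discussion sentence on smaller effects so that it covers only single-case effects of roughly 0.65 to 0.85 and above.
- In the RQ4 methods, state that a non-significant PDT for FSE does not show non-response.

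Pooling the 20 single-case estimates could be considered for smaller effects, but it is optional, answers a group-level question and is not part of this correction.

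The cost is one table cell, a few sentences and a less favourable stated figure. No extra participants, data collection or change to the RQ1 analysis is needed.

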#### RQ3: What is the pattern of change in the study outcomes at the single-case level?

We will conduct single-case change point analyses for participants in which significant changes in mean level or slope were detected by the PDT and/or ITSA (RQ2). Data will be analysed with Wild Binary Segmentation (WBS) [62]. WBS has no assumptions. It tests for change points by splitting the longitudinal observations into random intervals. Per individual, the analysis gives insight into the exact moment of change (both level and slope) for each outcome. This will provide us with information on which Booster intervention stages or elements were relevant to changes in the study outcomes across individuals. In the future, this information on effective intervention mechanisms could be used to improve the Booster intervention further.

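### The RQ3 change-point power has no effect size; at the small effects the protocol anticipates, a 10 to 18 day run-in will usually miss a change at the Start Conversation, and dating it exactly is overstated

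*Protocol article*

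**What the plan says.** Sample size {14} states for RQ3 that, for 80% power, "fifty measurements are needed, including at least six post-change points (start Phase B"). No effect size, error rate or autocorrelation is attached. The power statements for RQ1 and RQ2 in the same section do carry an effect size: 0.7 for the group-level randomisation test and 0.3 for the permutation distancing test. The paragraph then says of the run-in before T1 that it "enables us to detect whether the Start Conversation itself or the Measurement Period (T1 to T2) coincides with a change point".

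The same section says: "However, we anticipate small intervention effects since Booster is an early intervention, not treatment". The note to Table 1 defines small at the single-case level as 0.00 to 0.99 and medium as 1.00 to 2.49.

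The RQ3 section plans WBS for participants with a significant change in RQ2 and states: "Per individual, the analysis gives insight into the exact moment of change (both level and slope) for each outcome". It goes on to say that these dates will show which intervention stages or elements were relevant across individuals.

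**The concern.** A rule that counts observations has no power until a step size is named. This rule is illustrated with the change at the start of Phase B, where the protocol counts at least 42 earlier values. A change at T1 has only 10 to 18 earlier values at full compliance, or about 7 to 13 with 30% missing (0.7 × 10 = 7; 0.7 × 18 = 12.6). The count rule is still met, but it does not say whether so short a run-in can reveal a small shift.

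Two readings are at stake. If no change point is found at T1, a reader may conclude that the Start Conversation did nothing. If one is found, its date may be taken as identifying the stage that worked. The RQ3 section intends this information to guide further development of the intervention.

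**Working it through.** **Inputs from the protocol.** Autocorrelation: "Thus, we assumed the autocorrelation in our study to be 0.30 across outcomes". Series length: "With 100% compliance, the number of repeated measurements is 130". Run-in 10 to 18 days; Measurement Period 28 days; Experiment Period 84 days. Tolerated missingness is 30% (group level) or 40% (single case).

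**Assumptions.** One lasting step, measured in within-person SDs; AR(1) errors; days missing at random; 5% false positives, two-sided.

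**1. The protocol's own figure.** The 80% cannot be reproduced, because no step size is given. It can be inverted for 50 values split 44 / 6. With the change day known, power = Φ(d/SE − 1.96), so the smallest step with 80% power is (1.96 + 0.84) × SE = 2.80 × SE.
- Independent errors: SE = √(1/44 + 1/6) = 0.435, so d = 2.80 × 0.435 = 1.22.
- Autocorrelation 0.30, generalised least squares: d = 1.53.
- Day unknown, as in RQ3 (CUSUM simulation, autocorrelation 0.30): power is 13% at 0.7, 25% at 1.0, 53% at 1.5 and 81% at 2.0.

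On the protocol's own autocorrelation, the rule therefore gives 80% only near 2 SD when the day must be searched for.

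**2. Change at T1, day known (a favourable bound), full data.** The smallest step with 80% power is 1.20 / 1.04 / 0.94 SD for 10 / 14 / 18 days. At 0.7 SD and 10 days, SE = 1.20/2.80 = 0.43, and power = Φ(0.7/0.43 − 1.96) = Φ(−0.33) = 37%. For 14 and 18 days it is 47% and 55%.

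**3. Change at T1, day unknown, 30% missing.** Thresholds were set to 5% false positives under autocorrelation 0.30.

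| True step (SD) | CUSUM, 10 / 18 days | Calibrated WBS, 10 / 18 days |
|---|---|---|
| 0.3 | about 7–8% | about 6% |
| 0.7 | 16 / 27% | 9 / 14% |
| 1.0 | 27 / 53% | 17 / 34% |
| 1.5 | 62 / 90% | 38 / 73% |
| 2.5 | 98 / 100% | 92 / 100% |

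The last two rows come from a separate simulation with the same settings. At 0.99 SD that simulation gives 27 / 52% (CUSUM) and 12 / 31% (WBS), so the two agree to within a few points. Missing data are not the main cause: with complete data, WBS detects 9 / 17% at 0.7 SD and 20 / 37% at 0.99 SD.

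**4. Dating at T1.** With 30% missing, the share of all series in which CUSUM both detects the step and places it within 3 days is 6 / 10% at 0.7 SD and 15 / 26% at 0.99 SD (10 / 18 days).

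**5. Dating at T2.** This takes day 42 (14 + 28), 30% missing, CUSUM. Detection is about 51% at 0.7 SD and 83 to 85% at 1.0 SD. Among detected changes:

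| | 0.7 SD | 1.0 SD |
|---|---|---|
| Median date error | 0 days | 0 days |
| Middle half of errors | −6 to +9 days | −4 to +4 days |
| Within 3 days | about 33–35% | about 49–50% |
| Within 14 days | about 72% | about 83% |
| More than 14 days off | 100 − 72 = 28% | 100 − 83 = 17% |

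**The case against.** The protocol does not claim 80% power at T1. The sentence on the run-in gives no power there, and it can be read simply as the reason for having a run-in, since without earlier data a change at T1 could not be seen at all. That is right: a reader might infer a false 80% claim at T1, and the text does not support that inference. Nor does the run-in break the count rule; ten days with 40% missing still leave six values. What stands is that the sentence asserts detectability without limit, directly after a power rule with no step size, in a section that expects small effects.

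The rule rests on a cited source, and the timing on a supplementary figure; neither is at hand, and an effect size may be given there. Its absence alone would be a minor omission. The point rests on what the article affirms.

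A reader might also infer that RQ3 is the only route to when and through what Booster works. It is not. The protocol plans interviews to support interpretation of the single-case results, relates goal attainment to outcomes, and in the Discussion asks for replication across individuals together with alignment to stage timing. RQ3 is exploratory.

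It is tempting to say that dates scatter over weeks or usually fall in the wrong stage. The results do not show this. Typical errors are days and only the tails reach weeks; the share assigned to a wrong stage was not calculated.

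Finally, RQ3 is run only in RQ2 responders. The detection rates above are not conditioned on that selection, which would be expected to raise them by an amount not calculated here.

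**Conclusion.** The point holds in a limited form. Within the range the protocol calls small, a real step at T1 will usually be missed. With WBS and 30% missing, detection is about 6% at 0.3 SD, 9 to 14% at 0.7 SD and 17 to 34% even at 1.0 SD. Reaching 80% with WBS needs roughly 1.5 to 2 SD or more, depending on run-in length. Steps of 2.5 SD are found in at least 92% of series, so the run-in is adequate for large shifts. Change points found at 0.7 to 1.0 SD centre on the true day but are too uncertain to be called exact.

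The figures assume a single lasting step, AR(1) errors at 0.30 and days missing at random. The dating results at T2 come from CUSUM. The consequence is confined to the stage-level interpretation of RQ3; the group-level test is not affected.

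**What to change.** In Sample size {14}, state the step size to which the 80% refers, derived for WBS at autocorrelation 0.30 and the tolerated missingness. CUSUM-based figures should not be used, because they are too favourable for WBS. Limit the T1 sentence to larger shifts, and add that finding no change point at T1 does not exclude a small change there.

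In the RQ3 section, replace the claim to an exact date with an estimated change point and an uncertainty interval from a bootstrap that preserves the autocorrelation (block or AR). Attribute a change to a stage (before T1, Measurement Period or Experiment Period) only when the interval lies within that stage. Describe it as compatible with T1 or T2 when the interval covers that day. Otherwise report the stage as not identifiable.

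The cost is wording, one simulation for WBS and a bootstrap on data already being collected, so it remains feasible although recruitment began in October 2024. The downside is that fewer participants will have a stage attributed.
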